#### Sensitivity analyses for handling missing data in the primary endpoint

Missing data are expected to increase during the trial due to the COVID-19 pandemic. In the primary and key sensitivity analyses, pandemic-related missing data will be treated as all the other missing data.

In these additional analyses, according to the estimand framework [19], the treatment policy strategy is adopted for COVID-19 intercurrent events. In such approach, we consider the pandemic irrelevant in the effect estimate, and all collected data are used in the analyses. All missing data will be imputed by MI under MAR assumption, by including also COVID-19 infection status and pandemic time-period in the imputation model [25]. Moreover, under the assumption that the pandemic (restrictive measures, lockdown and infections) could negatively affect the outcome, the analysis under MNAR assumption will be repeated, conducting a tipping point analysis for COVID-19-related missing data. MI analysis will be conducted using the number of imputations and the pooling rule previously specified.

#### Sensitivity analysis for the secondary survival endpoint

As the pandemic may affect the survival probability, the proportional hazards assumption will be checked by visual assessment of Kaplan–Meier curves, log(− log) plots, and testing of scaled Schoenfeld residuals. If the assumption of proportional hazards between treatment groups is not verified, the ratio of restricted mean survival time between groups will be provided [18, 26, 27]. The infection status and the pandemic time-period will be included in the multivariable Cox model. Moreover, in case the number of censoring due to COVID-19 is not negligible, the treatment effect will be evaluated by using the inverse probability of censoring weighting method. The weights will be calculated by a logistic regression model considering baseline characteristics and time-dependent covariate such as the infection status and pandemic time-period [28, 29].

Finally, due to the reduction in sample size and consequently the decrease in power, an analysis assessing the association of the survival time with the disease progression (ALSFRS-R slope) will be conducted. We will perform the Cox multivariable regression, in which the primary exposure is the slope of ALSFRS-R score. The analysis will also be repeated considering the responder status as the main exposure.

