### Randomization

Patients are randomized 1:1 to receive TUDCA or placebo. After completing the lead-in period at month 0, eligible patients are randomized by means of a computerized central randomization system and coupled to a unique treatment code through an electronic platform. The randomization list has been generated using STATA software with the “ralloc” command. A permuted block randomization procedure, stratified by country, has been adopted to ensure balance across treatment groups.

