### Sample size

The study was powered to assess the potential benefit of TUDCA compared with placebo on the rate of progression, as measured by the ALS-FRS-R total score. The target number of participants was determined based on the expected proportion of responders. In the original planning, based on data from the phase II study [5], a sample size of 199 subjects per arm was calculated to detect a 10% difference between arms assuming a response rate of 10% in the placebo group. This sample size provides at least 80% power with a two-sided alpha of 5%. Considering a dropout rate of 10% at 18 months, a total sample size of 440 patients was planned. Such a sample size provides 83.3% power to detect a 13% absolute difference in survival (defined as death or respiratory insufficiency) between the two treatment groups, corresponding to a hazard ratio of 0.616, assuming an 18-month survival of 60% in the placebo group. However, due to the impact of the COVID-19 outbreak on recruitment [9], the enrolment was planned to be closed at 320 randomized patients. The reassessed sample size allows us to detect an absolute difference of 11% in the proportion of responders between the TUDCA and the placebo arms. It also provides a power of 80% to detect a 14% absolute difference in survival, corresponding to a hazard ratio of 0.58.

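### The restricted mean survival time ratio is reported only if a low-powered, data-dependent check rejects proportional hazards; report it in every case

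*SAP article*

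**What the plan says.** In the SAP article, the section on sensitivity analysis for the secondary survival endpoint plans to check proportional hazards by "visual assessment of Kaplan–Meier curves, log(− log) plots, and testing of scaled Schoenfeld residuals". The consequence follows directly: "If the assumption of proportional hazards between treatment groups is not verified, the ratio of restricted mean survival time between groups will be provided". The article gives no test level, no time scale for the residual test, no rule for combining plots and test, and no RMST horizon.

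The section on analysis methods for primary and secondary outcomes plans Kaplan–Meier analysis, the log-rank test, univariate and multivariable Cox models, and a joint-model omnibus test of ALSFRS-R and survival. None of these depends on the check.

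The Sample size section gives the planning figures: "the enrolment was planned to be closed at 320 randomized patients", placebo survival "assuming an 18-month survival of 60% in the placebo group", and for the reduced trial "It also provides a power of 80% to detect a 14% absolute difference in survival, corresponding to a hazard ratio of 0.58".

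**The concern.** The gate treats a failure to detect non-proportional hazards as enough reason to leave out the one effect measure that would be valid without that assumption. A residual test on about 100 events has limited power, so passing it says little. The visual part has no stated criterion and is judged on the observed curves. Whether RMST appears therefore depends on the data and partly on the analyst's eye, although the abstract gives the avoidance of data-driven analysis as a purpose of the article.

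If the effect is delayed or wanes and the check does not flag it, the only between-arm effect size for survival is a Cox hazard ratio. That ratio averages phases with different effects and may describe none of them. RMST over 18 months keeps its meaning in either case.

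**Working it through.** **Inputs from the SAP article.** 320 randomized, 1:1, so 160 per arm; placebo 18-month survival 60%; planned difference 14 points, so 74% on TUDCA; planned hazard ratio 0.58; alpha "with a two-sided alpha of 5"%; dropout 10% at 18 months; follow-up 18 months.

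**Assumptions, not in the article.** Exponential placebo hazard; 5% level for the residual test; the delay lengths and late hazard ratios below.

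**Step 1: reproduce the plan's power.** Events without dropout = 160 × (0.40 + 0.26) = 105.6. Schoenfeld power = Φ(|ln 0.58| × √105.6 / 2 − 1.96) = Φ(2.80 − 1.96) = 79.9%, which matches the stated 80%. For the earlier target of 440 patients: 220 × (0.40 + 0.27) = 147.4 events, and a hazard ratio of 0.616 gives 83.7% against the stated 83.3%. If dropouts contribute no events, 105.6 × 0.9 = 95; with exponential dropout the count is about 102. About 100 events is a fair working figure.

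**Step 2: power of the residual test.** Simulated trials with 160 per arm, administrative censoring at 18 months, Cox model with treatment only, and a scaled Schoenfeld residual test on untransformed time. Under proportional hazards the test rejects in about 5%, as it should.

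| Pattern of hazard ratio | Rejects, no dropout | Rejects, 10% dropout | Average Cox HR (10% dropout) |
|---|---|---|---|
| 1 for 3 months, then 0.5 | 21% | 18% | 0.60 |
| 1 for 3 months, then 0.4 | 29% | 29% | 0.52 |
| 1 for 6 months, then 0.5 | 32% | 32% | 0.70 |
| 1 for 6 months, then 0.4 | 49% | 46% | 0.63 |
| 1 for 9 months, then 0.5 | 34% | 30% | 0.78 |
| 1 for 9 months, then 0.4 | 48% | 45% | 0.75 |
| 0.4 to month 9, then 0.8 | not run | 28% to 30% | 0.57 |
| 1 for 9 months, then 0.3 | 67% | 63% | 0.69 |
| 1 for 9 months, then 0.2 | 83% | 81% | 0.65 |

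The miss rate is 100% minus the rejection rate. For late hazard ratios of 0.4 to 0.5 it runs from 51% to 82%; for the waning pattern it is 70% to 72%; for 9 months then 0.3 it is 33% to 37%. Kaplan–Meier or rank time changes power by at most 7 points. Log time raises it by up to 12 points for a 3-month delay and lowers it by up to 28 points for the longer delays.

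**Step 3: what RMST would add.** Hold 18-month TUDCA survival at the planned 74% and compare two patterns.
- Placebo: hazard λ = −ln 0.60 / 18 = 0.02838 per month; RMST = 0.40 / 0.02838 = 14.1 months.
- TUDCA, proportional hazards: hazard = −ln 0.74 / 18 = 0.01673; RMST = 0.26 / 0.01673 = 15.5 months; ratio 1.10.
- TUDCA, no effect for 6 months: the late hazard ratio must be (0.3011 − 6λ) / (12λ) = 0.38. Survival at 6 months is 0.843. RMST = (1 − 0.843)/0.02838 + (0.843 − 0.74)/(0.384 × 0.02838) = 15.0 months; ratio 1.06.

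The Cox hazard ratios are close, about 0.58 and 0.61, yet in the second pattern the true ratio is 1 and then 0.38. The residual test rejects in about 51% of such trials (44% on log time).

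**The case against.** The gate is less decisive than it may appear, and four stronger readings do not hold.

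- **That the hazard ratio would stand alone.** It would not. Kaplan–Meier curves, the log-rank test and the joint model are reported whatever the check shows, and a late separation would be visible in the curves.
- **That the check decides between RMST and the Cox model.** The text adds RMST if the assumption fails; it does not say that RMST replaces the Cox model.
- **That the miss rates above are the rates at which RMST would be withheld.** They describe the residual test alone. A poor plot could also count as the assumption not being verified, so the true rate cannot be computed. A condensed article may leave the test level and the combining rule to the full plan, and I do not count their absence as an error.
- **That any strong delayed effect is missed half the time or more.** After 6 or 9 months without effect, late hazard ratios of 0.2 to 0.3 are missed in only 12% to 33% without dropout (untransformed time).

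The pandemic is also weak evidence for the patterns simulated. It runs in calendar time, and randomization ran from May 2019 to April 2022, so a given pandemic period falls at different follow-up times for different patients. The article does not say that a delayed effect is expected.

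All of this stands and limits the size of the point. It does not justify the gate: the test has low power for moderate departures, and the visual step leaves the decision open until the curves have been seen.

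**Conclusion.** The point holds as a minor one. The only named between-arm survival effect measure that is free of proportional hazards depends on a check whose formal part misses roughly 50% to 80% of moderate departures at about 100 events, and about a third of one stronger late departure (9 months, then 0.30). Because the plots may also trigger RMST, the overall trigger rate is unknown. What may be lost is one summary measure for a secondary endpoint. The primary responder analysis and the log-rank test are unaffected.

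The figures rest on an exponential placebo hazard, a 5% test level, untransformed time and the chosen patterns. On log time the 9-month, 0.30 case would be missed more often (57% to 60%).

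**What to change.** Replace the conditional sentence with an unconditional one: the 18-month RMST ratio and difference between arms, each with a 95% confidence interval, are reported as supplementary estimates beside the log-rank test and the Cox hazard ratio. Keep the Kaplan–Meier and log(−log) plots and the Schoenfeld test as a description of how well proportional hazards fits, with no decision attached.

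The cost is one sentence in the SAP and one further secondary result (ratio and difference) to report, from data already being analysed. The log-rank test, the Cox models and the sample size do not change.

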## Analysis

### Outcomes

The primary outcome is measured through the identification of the responder patients, defined as those showing an improvement of at least 20% in the ALSFRS-R slope during the 18-month randomization period compared to the 3-month lead-in period. Slope coefficients for ALSFRS-R decline will be calculated separately for the lead-in period and the treatment period using the linear regression model.

The secondary efficacy outcomes are presented in Table 2. The safety and tolerability of TUDCA will be evaluated through the assessment of adverse events, concomitant treatments, physical examinations, vital signs, and routine laboratory tests (hematology and biochemistry).

**Table 2 Tab2:** Secondary and exploratory outcomes

Variable	Description

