**Clinical**	
ALSFRS-R score (*ALSFRS-R)*	ALS Functional Rating Scale Revised consists of 12 questions, each scored out of 4 points. A total score is calculated by summing the scores from each question with a maximum score of 48 (better performance, i.e., absence of the measured symptoms of ALS) and a minimum score of 0 (worst performance)
Survival time measured by death or respiratory insufficiency	Survival status is recorded at the end of study as well as respiratory insufficiency defined as tracheostomy or the use of non-invasive ventilation for ≥ 22 h per day for ≥ 10 consecutive days. Survival time is defined as the time elapsed between randomization and death from any cause and tracheostomy, whichever occurs first
Forced vital capacity score (FVC)	The index of respiratory function expressed as a percentage of the expected value is used to indicate potential respiratory compromise
Muscle force assessed by the Medical Research Council (MRC) scale	MRC score is a summation of the strength of 6 muscle groups tested on both sides ranging from 0 (paralysis) to 60 (normal strength)

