### Missing data

#### Imputation rules and key sensitivity analyses

In the primary analysis, for each patient, all available ALSFRS-R scores will be included in the linear regression model to estimate the monthly decline. The following rules for handling missing data will be applied: (i) for deceased patients, as death is clearly a poor outcome and there is no consensus on an alternative score, the lowest score (zero) will be assigned at the time of death, and (ii) for withdrawals or LTF patients without a post-randomization assessment of the ALSFRS-R score, the monthly decline of ALSFRS-R will be imputed using the “nearest neighbor” procedure [15]. For each of these subjects, we will identify the five other participants within the same treatment group whose baseline ALSFRS-R scores were closest to the baseline score of the patient. Then, the largest monthly ALSFRS-R decline observed among the identified neighbors (worst-case imputation) will be used for imputation. All missing data will be imputed within treatment groups defined by the randomized treatment assignment. As sensitivity analysis, within the nearest neighbor procedure, the “bestcase imputation” will also be carried out imputing the smallest observed monthly decline.

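### The Cox model of survival on ALSFRS-R slope and responder status uses exposures that include a zero scored at death, so death helps to build its own predictor

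*SAP article*

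**What the plan says.** The last paragraph of *Sensitivity analysis for the secondary survival endpoint* gives reduced power as the reason for relating survival time to disease progression. The model is stated as "We will perform the Cox multivariable regression, in which the primary exposure is the slope of ALSFRS-R score", followed by "The analysis will also be repeated considering the responder status as the main exposure". That paragraph does not say which slope is meant, sets no landmark and does not treat the exposure as time-dependent.

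The exposures are built elsewhere:

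- *Outcomes*: "Slope coefficients for ALSFRS-R decline will be calculated separately for the lead-in period and the treatment period using the linear regression model". Responders are "defined as those showing an improvement of at least 20% in the ALSFRS-R slope during the 18-month randomization period", relative to the lead-in.
- *Imputation rules and key sensitivity analyses*, for the primary analysis: "all available ALSFRS-R scores will be included in the linear regression model to estimate the monthly decline". For patients who die, "the lowest score (zero) will be assigned at the time of death".
- Table 2, survival row: "Survival time is defined as the time elapsed between randomization and death from any cause and tracheostomy, whichever occurs first".

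**The concern.** Read together, these sections put the outcome inside the predictor. A death is an event in the Cox model. The same death adds a zero to that patient's regression, steepens the fitted decline and almost always makes the patient a non-responder. Patients who survive get no such point. Separately, a slope fitted over the whole treatment period is not known at randomisation, when the survival clock starts, and it rests on fewer scores in patients who die early.

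At stake is how the result will be read. A strong association between responder status and survival could be taken as showing that the responder endpoint tracks survival, when much or all of it could come from the scoring rule.

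**Working it through.** **The plan's own survival figure.** The analysis at issue has no stated figure. The survival power beside it reproduces. Inputs from *Sample size*: N = 320, placebo survival 60%, difference 14 points (so 74%), hazard ratio 0.58; two-sided 5%, no dropout.

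- Events = 320 × (0.40 + 0.26)/2 = 105.6.
- Power = Φ(√105.6/2 × |ln 0.58| − 1.96) = Φ(2.80 − 1.96) = Φ(0.84) = 79.9%, against the stated 80%.

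**What one zero does to a slope.** Take scores 38, 35, 32 at months 0, 3, 6, a true decline of 1 point/month, and death at month 7.

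- Times 0, 3, 6, 7 have mean 4; deviations −4, −1, 2, 3; sum of squares 30.
- Slope = (−4×38 − 1×35 + 2×32 + 3×0)/30 = −123/30 = −4.1 points/month.

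Now take a patient whose lead-in decline was 1 point/month and who then scores 38, 37, 36, a decline of 1/3 point/month and so well beyond a 20% improvement. With death at month 7 the slope is (−152 − 37 + 72 + 0)/30 = −3.9. Response needs a decline of at most 0.8, so this patient is a non-responder only because of the zero.

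**Simulation with no true association.** From the documents: 320 patients, three-monthly visits, the lead-in and treatment slopes, the 20% threshold and the zero at death. Assumed: baseline score 38 (SD 5), lead-in decline 1 point/month (SD about 0.6), measurement SD 1.5, constant hazard independent of decline, 66.5% overall 18-month survival (320 × 0.335 ≈ 107 events), and deaths forming 25–100% of events. There were 150 trials per scenario, with likelihood-ratio tests at 5%. A true rate of 5% therefore carries Monte Carlo error of about 1.96 × √(0.05 × 0.95/150) = 3.5 points.

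Entries are the percentage of trials significant; HR is the median for responders.

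| Scenario | Slope, with zero | Responder, with zero | Slope, no zero | Month-6 landmark: slope / responder |
|---|---|---|---|---|
| All events deaths | 100 | 100 (HR 0.036) | 14 | 10 / 5 |
| 75% deaths | 100 | 100 (HR 0.21) | 9 | 7 / 5 |
| 50% deaths | 100 | 96 (HR 0.41) | 10 | 5 / 6 |
| 25% deaths | 100 | 51 (HR 0.64) | 11 | 3 / 5 |
| All deaths, decline 1.5 times faster after randomisation | 100 | 100 (HR 0.043) | 39 | 5 / 2 |
| All deaths, 85% survival | 100 | 100 (HR 0.040) | 15 | 7 / 7 |

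In the first scenario about 2% of deceased patients counted as responders. Responder status without the zero was significant in 4–7% of trials. Other simulations under similar assumptions gave 100% for the slope with the zero. For responder status at 25% deaths they gave HR 0.68–0.70, significant in 33–42% of trials.

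**Why no slope hazard ratio is given.** A score of 38 at month 0 followed by a zero at month 0.1 gives a slope of 38/0.1 = 380 points/month. A few such patients dominate the estimate, and its median differed severalfold between runs. Only the rejection rate is stable.

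**The case against.** Four stronger readings are tempting, and the documents do not support them.

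- *The plan states that the slope exposure contains the zero.* It does not. The zero rule is written for the primary analysis, and the survival section says only that the slope is used. Another source is conceivable, such as the mixed model or the imputation analysis that penalises deaths, but the section points to neither. Carry-over is therefore the natural reading for slope. For responder status it follows from the main definition.
- *The analysis will show a huge association whatever the data.* This is too strong. Zero is assigned only at death, while tracheostomy also counts as an event. With a quarter of events being deaths, the spurious responder effect is moderate and often not significant.
- *The analysis is meant to support a survival claim for TUDCA.* The plan speaks of association and attaches no decision rule. The log-rank and Cox comparisons of the arms do not use these exposures.
- *The planned joint model already supplies the answer.* *Analysis method for primary and secondary outcomes* names an omnibus test of the simultaneous effect on ALSFRS-R and survival. It does not say that the slope–survival association will be estimated.

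It can also be said that the article condenses a fuller SAP, which may define the exposure window. That is possible, but the article names both the exposures and the model, and on its own definitions the combination is circular. Nor does a genuine link between decline and survival rescue the analysis, since it would give a significant slope result whether or not the link existed.

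**Conclusion.** The point holds for one supplementary analysis and should be corrected. With the zero included, the slope model rejected in 100% of null trials in every scenario. The responder model rejected in about 33–51% (HR about 0.64–0.70) with a quarter of events being deaths, rising to 100% (HR about 0.04) when all are. Removing the zero is not enough for slope: about 8–39% false positives remain across runs, because the exposure still spans the follow-up it is meant to predict.

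These figures rest on the assumed score distribution, a constant hazard and the share of deaths, none of which the document gives. Simulated responder rates without the zero were 22–40%, above the 10% planned for placebo. The direction of the bias does not depend on these choices; the responder hazard ratio does.

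**What to change.** In the last paragraph of *Sensitivity analysis for the secondary survival endpoint*:

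1. State which slope is used, and exclude the zero-at-death score from any exposure in this analysis.
2. Use a landmark. For example, compute slope and 20% response from observed month 0–6 scores in patients event-free at month 6, and count survival from month 6, with later landmarks as sensitivity. Month 6 is an example; what matters is fixing it in advance. Error was near 5%, 2–10% across runs.
3. Alternatively, use a joint or time-dependent model and add the slope–survival association as an estimated quantity.
4. Report the result as association only.

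The cost is a wording change and a small program change. Events before the landmark are not used: under a constant hazard with 66.5% survival, 320 × (1 − 0.665^(1/3)) ≈ 41 of about 107 events fall before month 6. The slope rests on three scores, and response is measured over a shorter window than the primary definition, so this responder variable is not the primary endpoint and should be labelled as such.
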